## Abstract

**Background:**

Wearable monitoring devices, such as smartwatches and fitness bands, are health technologies for enhancing self-care management among community-dwelling older adults. While the evidence suggests that these devices can promote health, older adults often struggle to use them over the long term. Community health workers can effectively motivate older adults to change their health behaviors. This study proposes an intervention involving community health workers as peer supporters to promote sustained daily use of wearable monitoring devices among community-dwelling older adults.

**Methods:**

The intervention group in this randomized controlled trial will receive the Live with Wearable Monitoring Device program from trained community health workers with the support of a nurse and social workers through a one-time home visit and regular phone calls. The control group will receive only the wearable monitoring device. Data will be collected at baseline, 1 month, 3 months, and 6 months.

**Discussion:**

Merely providing older adults with wearable monitoring devices may not lead to the realization of the potential health benefits of these devices, as long-term usage can be challenging. The results of this trial can provide evidence for a new approach to enhancing self-management and community healthcare among community-dwelling older adults, ultimately improving their health outcomes.

**Impact:**

Wearable monitoring devices not only enable real-time monitoring of vital signs, but can also support tailored messaging and facilitate virtual communication between users and healthcare professionals. Despite considerable health benefits, there is evidence showing that older adults largely stop using them after a few months. This study is the first to use a peer support approach to help older adults incorporate a wearable monitoring device in their daily routines in conjunction with goal setting and regular reminders. This will boost the self-care ability of the older adults, allowing them to continue physically functioning in the community.

**Trial registration:**

This study was prospectively registered at clinicaltrials.gov (identifier: NCT05269303). Registration date: 24/2/2022.

## Introduction

Aging populations are a growing global phenomenon. There are currently about 1 billion people above the age of 60, a figure that is projected to increase to more than 2 billion, or about 22% of the total population, by 2050. Older adults commonly have chronic health conditions such as hypertension and diabetes, and require long term self-care management to prevent hospitalization and maintain their ability to live in the community [1]. There is promising evidence to show that self-care management strategies such as education [2] and self-monitoring [3] can promote better health outcomes among older adults. These self-care management strategies are now widely achievable using wearable monitoring devices (WMDs). WMD is a type of digital health technology that can be used for remote monitoring and has the potential to empower older adults in managing their self-care behaviors and improving their physiological and psychosocial health through early detection and prevention, while allowing them to live at ease in their own community.

WMDs such as fitness bands and smartwatches, which can be worn on the wrist, have sensors capable of detecting and recording physiological health data such as heart rate, step numbers, and the duration and intensity of an individual’s physical activity [4–6]. The data that are collected can be transmitted through a wireless sensor network to the server of a service provider for automatic processing, to provide immediate feedback to the user. The primary doctors and nurses of the users could also monitor the health data in real time and provide immediate, individualized feedback to the users. [7]. The evidence has shown that the use of WMDs can increase disease self-efficacy [8], enhance physical performance in daily activities [9], lower the incidence of falls [10], and increase physical activity [11] among older adults with chronic diseases.

Despite the benefits, recent reports have found that older adults have difficulty maintaining the long-term use of WMD. A study investigating the attitudes of older adults towards WMD has shown that 60% of participants stopped using the device after two weeks [12]. Another study aimed at investigating the effectiveness of WMD on the frequency of physical exercise showed that more than 20% of the older participants stopped using the WMD during the 12-week intervention period and another 50% discontinued the use of device 6 weeks after the intervention [13]. In fact, barriers such as the absence of clear instructions, knowledge, and support on handling the device, and a lack of motivation in learning new things have prevented older adults from continuing the use of WMDs [14].

Community Health Workers (CHW) have been recognized as paid workers who can motivate and support older adults in adhering to health-promoting and self-management activities. A qualitative study revealed that CHWs played a crucial role in facilitating the monitoring of vital signs, promoting physical exercise, and providing health education on older adults with chronic diseases [15]. In fact, CHWs do not necessarily have a professional medical or psychosocial background but do have commonalities with the person they are providing care to, such as age, socioeconomic background, and living place, which allow them to easily build strong rapport and connection with the care recipient [16]. In one study, older adults commented that they felt a sense of understanding, caring, and companionship from their CHW. They were more resilient to set-backs and more motivated to learn because their CHW was able to provide nonjudgmental support [17]. Previous studies discovered that a CHW-led program not only has significant effects on improving health outcomes for older adults [18], but is also cost-effective [19].

Compared with healthcare providers, CHWs are more familiar with the older adults and have more free time to teach them how to use the health features of the WMD and to overcome technical difficulties. There is, however, no study evaluating the effectiveness of CHW-led intervention programs on the sustained use of technological devices, including WMD, among community-dwelling older adults. In a pilot study in India, a training program was designed for CHWs to promote the use of WMDs to the public, but there was no data on the rates of usage and adherence [20]. The Live With Wearable Monitoring Device (LWMD) program is the first to integrate a peer support model to motivate older adults to sustain their use of a WMD for health monitoring and self-care management. This new approach has the potential to encourage the older adults to prolong and sustain their use of the device, thereby improving their long-term health and quality of life, and reducing their use of tertiary healthcare services.

There are three objectives in this study:

Assess the usability of the WMD from the perspective of older adults, including facilitators and barriers to the use of the device, level of satisfaction with the safety, convenience, and features of the device, attitude towards the use of the device, the perceived usefulness of the device, its perceived ease of use, and self-efficacy and level of anxiety in using the device.Evaluate the feasibility of the Live With Wearable Monitoring Device program, including the recruitment rate, attrition rate, adverse events, and technical difficulties.Identify the preliminary effectiveness of the LWMD program among older adults dwelling in the community, including their quality of life, utilization of health services, sustained use intention, and rate of adherence.

### Conceptual framework

This study was designed with reference to the Self-Determination Theory (SDT) [21]. According to this theory, people are more likely to adopt a particular behavior if they have an intrinsic motivation to carry out that behavior. Intrinsic motivation is influenced by three factors: autonomy, competence, and relatedness. Autonomy represents a sense of control over the behavior. Competence represents the perceived feeling of mastery of the behavior. Relatedness represents a feeling of being socially connected with people who share the same interest in the behavior. This study will provide options for older adults to integrate WMD into their daily life, educate them on the necessary knowledge and skills to operate the WMD, as well as strengthen the social connection and support from the CHWs.

## Research plan and methodology

### Study design

A randomized controlled trial design will be adopted in this study. The SPIRIT statement was used as a guideline for this protocol paper (Fig 1).

**Fig 1 pone.0294517.g001:**
[figure not shown]
The schedule of enrolment, interventions, and assessments.

### Study setting, subjects, and recruitment strategies

The recruitment will be carried out in five community centers. Members of the community centers who have shown an interest in this program will be screened and recruited. The inclusion criteria are: (1) 60 years old or older, (2) owning a smartphone, (3) able to communicate in Cantonese or Mandarin, and (4) able to access the internet. The exclusion criteria are: (1) having a medically diagnosed cognitive impairment, (2) being bedbound, (3) already own a WMD, and (4) involved in other WMD-related studies.

A research assistant will explain details of the study to the eligible subjects. The written consent of the participants and their baseline data will be collected at the community centers. The participants will be randomly assigned to either the intervention or control group using group assignments generated by the Research Randomizer software. The group assignments will be sealed and opened sequentially by the principal investigator at the time of randomization. To maximize the level of double-blinding, participants will be informed that the intervention aimed to promote the use of the WMDs but will not be informed about their specific assignment to the intervention or control group. Furthermore, the research assistant responsible for data collection will remain blinded to the group allocation, while the providers, including community center staff, will not be blinded.

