#### Intervention group

The subjects in the intervention group will receive a three-month program called Live With Wearable Monitoring Device (LWMD), which will be conducted by CHWs under the supervision of our research nurse. The nurse and the trained CHWs will provide a first home visit session to subjects in the first month. The nurse will use the Omaha System, an evidence-based and comprehensive tool widely used in community-based practice, to identify physical and psychosocial health problems among the subjects that could be prevented or resolved through the use of the WMD [22]. For instance, the nurse will assess ten problem areas of the Omaha System, utilizing functions such as blood pressure and pulse monitoring in the WMD. These problem areas include role change, interpersonal relationships, mental health, pain, respiration, sleep and rest patterns, circulation, physical activity, substance use, and medication regimen (Fig 2).

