**Fig 2 pone.0294517.g002:**
[figure not shown]
The problems of the Omaha System that linked with the blood pressure and pulse monitoring feature of the WMD.

In the event of abnormalities being detected, the nurse will suggest that participants utilize specific features of the WMD that are relevant to their identified health and social problems. They will provide recommendations regarding the duration and frequency of usage, as well as instructions on how to incorporate these features into their daily routines.

The CHWs will support the nurse with health assessments and the setting up of goals and action plans, and play an active role in communicating between the nurse and the subjects during the home visit. Starting from the third week, they will make regular phone calls to the subjects every other week until the twelfth week, to remind and encourage them to use the WMD. During the phone call, they will follow up on the problems that were identified by the nurse, on the subjects’ progress in attaining the goals, and suggest solutions for tackling the barriers preventing the subjects from implementing the action plans. The CHWs will seek help from the nurse when there is a need to modify the goals and action plan, or when any health issues arise that cannot be solved by the CHWs [23,24].

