#### Control group

Subjects in the control group will use the WMD by themselves. They will not receive services from the CHWs and the research nurse unless abnormalities are detected by the WMD (e.g., abnormally high blood pressure), in which case the nurse will follow up on the subjects according to the protocols.

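### The criteria do not stop two members of one household from being randomised to opposite arms, so a co-resident control could be partly exposed to the program

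*Protocol article*

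**What the plan says.** All references are to the protocol article.

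- **Who can enter** (Study setting, subjects, and recruitment strategies). "The recruitment will be carried out in five community centers". On inclusion: "The inclusion criteria are: (1) 60 years old or older, (2) owning a smartphone, (3) able to communicate in Cantonese or Mandarin, and (4) able" (the fourth item is internet access). On exclusion: "The exclusion criteria are: (1) having a medically diagnosed cognitive impairment, (2) being bedbound, (3) already own a WMD, and (4) involved in other WMD-related" (the fourth item is taking part in other research on such devices). None of the eight criteria concerns the household.
- **Unit of randomisation** (same section). "The participants will be randomly assigned to either the intervention or control group using group assignments generated by the Research Randomizer software". No household or other cluster unit is mentioned. Subjects are not to be told which arm they are in.
- **Program contacts.** The abstract's Methods paragraph says that the program is given "through a one-time home visit and regular phone calls". Under Intervention group: "The nurse and the trained CHWs will provide a first home visit session to subjects in the first month". The nurse advises on device features, on how long and how often to use them, and on fitting them into the day; the CHWs help to set goals and action plans. For the calls: "Starting from the third week, they will make regular phone calls to the subjects every other week until the twelfth week".
- **Control condition** (Control group). Controls use the device on their own. "They will not receive services from the CHWs and the research nurse unless abnormalities are detected by the WMD".
- **Sample size.** Effect size 0.72, alpha 0.05, power 80%, 32 per group, raised to 35 per group (70 in total) for drop-out. Nothing is allowed for exposure of controls to the program.

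**The concern.** Both arms get the same device, blood pressure monitor, pulse oximeter and 60-minute training session. What separates them is the support: advice on use, routines, goals, reminders and encouragement. Some of that can pass between people who live together. In a split household the nurse and CHW visit the control's own home, and the control may be present.

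Two things are at stake. First, a partly exposed control moves towards the intervention group, so the difference in usability, sustained use intention and wear time is pulled towards zero. Analysis by allocated group, whether by generalized estimating equations or their weighted form, does not undo this. Second, a couple in which one partner is visited and called and the other is not can work out the allocation that the plan withholds. The usability scales and sustained use intention are self-reported.

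The article's own limitations paragraph says that Chinese users are inclined to be more open to social influence in taking up such devices. That makes some sharing within a household plausible.

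**Working it through.** **Inputs from the article:** effect size 0.72; alpha 0.05, two-sided; power 80%; 32 per group analysed; 70 randomised, 35 per arm.

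**Assumptions (not in the article):** the share of subjects who enrol as co-resident pairs, and g, the fraction of the program effect that passes to an exposed control. I take g = 0.5 and g = 1.

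**Step 1: the plan's own figure.** A two-sample t-test with effect 0.72, two-sided alpha 0.05 and 80% power needs 31.27 per group, rounded up to 32, as stated. Power at 32 per group is 80.9%, so there is almost no reserve.

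**Step 2: chance that a pair is split.** With 35:35 allocation, once one member is placed, 35 of the other 69 places are in the opposite arm: 35/69 = 0.507.

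**Step 3: share of controls exposed.** Each split pair exposes one control, so f = (pairs × 35/69)/35 = pairs/69.

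- 10% of 70 subjects in pairs = 3.5 pairs: 1.78 split, f = 5.1%
- 20% = 7 pairs: 3.55 split, f = 10.1%
- 40% = 14 pairs: 7.10 split, f = 20.3%

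**Step 4: diluted effect and power.** Observed effect = 0.72 × (1 − f × g). Power is for the same t-test at 32 per group. The last column is the number per group, before drop-out, that restores 80% power.

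| Subjects in pairs | f | g | Effect | Power | n per group for 80% |
|---|---|---|---|---|---|
| none | 0 | – | 0.72 | 80.9% | 32 |
| 10% | 5.1% | 0.5 | 0.70 | 78.9% | 33 |
| 10% | 5.1% | 1 | 0.68 | 76.8% | 35 |
| 20% | 10.1% | 0.5 | 0.68 | 76.8% | 35 |
| 20% | 10.1% | 1 | 0.65 | 72.2% | 39 |
| 40% | 20.3% | 0.5 | 0.65 | 72.2% | 39 |
| 40% | 20.3% | 1 | 0.57 | 61.8% | 49 |

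With a single pair, f = 1/69 = 1.4%. Even with full transfer the effect is then 0.71 and power 79.8%.

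The sum shifts the control mean only; it ignores any change in spread and any correlation within pairs. It uses the usability effect on which the sample size rests. The article gives no power basis for wear time or sustained use intention.

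**The case against.** The case against is substantial, and much of it stands.

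- **Exposure is possible, not shown.** A reader might infer that some controls will be exposed and that the difference will shrink. No part of the article mentions couples, siblings or co-enrolment. The text supports *could*, not *would*.
- **The program is not mainly delivered in the home.** There is one home visit. The recurring contact is by telephone and is directed to the individual subject.
- **The content is tailored.** The nurse works from each subject's own problems, and the goals and plan follow from those. A co-resident may overhear advice but gets no assessment, plan or calls. General device skills are already taught in both arms. Full transfer is therefore an upper bound.
- **The control-group rule is not broken.** A reader might infer that the rule against CHW and nurse services for controls cannot be kept in a split household. A visit to someone else in the home is not a service to the control. It is a possible route of contamination, not a breach.
- **The loss may be small.** In the mildest tabled case power falls by two points, and the larger losses need many pairs, strong transfer, or both.
- **A full protocol may hold a household rule.** This is possible. But the article sets out its criteria as numbered lists that read as complete, and the point concerns what those lists permit.

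What survives is that the stated criteria and individual allocation leave this route open, that any spill-over acts towards no difference, and that the planned power has almost no room for it.

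**Conclusion.** The point holds as a gap in the design, not as a demonstrated bias. Co-residents can be split between arms, and a control in such a household could be partly exposed and could infer the allocation.

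The size rests on two quantities that the article does not give. With 10% of subjects in pairs, power at 32 per group goes from 81% to about 77–79%; with 20%, to about 72–77%. The 62% in the last row of the table needs 40% of subjects in pairs together with full transfer, and should not be read as an expected loss. With one or two pairs the effect is negligible. This is a cheap improvement to make before randomisation, because exposure in a split household cannot be reversed afterwards.

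**What to change.** Under Study setting, subjects, and recruitment strategies, add a fifth exclusion criterion: *living in the same household as a person already enrolled in this study*. Ask about it at screening.

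This sets f to 0 for the household route, so the effect of 0.72 and the 32 per group stand as planned. The cost is one criterion and one question. A few otherwise eligible members are turned away, and recruitment may be slightly slower.

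An alternative that turns nobody away is to randomise by household, but the analysis must then handle the clustering. Neither option addresses contact between the arms at the five centers, from which both arms are recruited.

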### Intervention

All subjects, regardless of whether they have been allocated to the intervention or control group, will be given a package that contains a WMD called ProVista Care®, a prepaid SIM card, a blood pressure monitor, and a pulse oximeter.

The WMD offers features that include vital signs monitoring, uploading, and recording, fall detection, location tracking, activity recording, medication and medical follow-up reminders, and phone calling. The subjects can upload their vital signs to the server of ProVista Care® and its smartphone application after measuring them using a blood pressure monitor and pulse oximeter. If abnormalities are detected, a research nurse in our program will follow up with the subjects via phone, based on protocols that have been developed in accordance with the guidelines of the National Institute for Health and Care Excellence. When deemed necessary, the nurse will make referrals to the emergency department, outpatient department, or hospital, based on their professional judgment and the established referral criteria.

All CHWs and subjects will receive a 60-minute training session on the use of the WMD, blood pressure monitor, pulse oximeter, and ProVista Care® app. The research team will also provide technical support throughout the study by leaving a hotline number in the community center.

#### Intervention group

The subjects in the intervention group will receive a three-month program called Live With Wearable Monitoring Device (LWMD), which will be conducted by CHWs under the supervision of our research nurse. The nurse and the trained CHWs will provide a first home visit session to subjects in the first month. The nurse will use the Omaha System, an evidence-based and comprehensive tool widely used in community-based practice, to identify physical and psychosocial health problems among the subjects that could be prevented or resolved through the use of the WMD [22]. For instance, the nurse will assess ten problem areas of the Omaha System, utilizing functions such as blood pressure and pulse monitoring in the WMD. These problem areas include role change, interpersonal relationships, mental health, pain, respiration, sleep and rest patterns, circulation, physical activity, substance use, and medication regimen (Fig 2).

**Fig 2 pone.0294517.g002:**
[figure not shown]
The problems of the Omaha System that linked with the blood pressure and pulse monitoring feature of the WMD.

In the event of abnormalities being detected, the nurse will suggest that participants utilize specific features of the WMD that are relevant to their identified health and social problems. They will provide recommendations regarding the duration and frequency of usage, as well as instructions on how to incorporate these features into their daily routines.

The CHWs will support the nurse with health assessments and the setting up of goals and action plans, and play an active role in communicating between the nurse and the subjects during the home visit. Starting from the third week, they will make regular phone calls to the subjects every other week until the twelfth week, to remind and encourage them to use the WMD. During the phone call, they will follow up on the problems that were identified by the nurse, on the subjects’ progress in attaining the goals, and suggest solutions for tackling the barriers preventing the subjects from implementing the action plans. The CHWs will seek help from the nurse when there is a need to modify the goals and action plan, or when any health issues arise that cannot be solved by the CHWs [23,24].

